**Fig. 2 Fig2:**
[figure not shown]
Criteria for diagnosis of osteoradionecrosis (ORN) in the Hyperbaric Oxygen for the Prevention of Osteoradionecrosis (HOPON) trial [24]. ORN, further classified [23]: Notani 1: ORN confined to alveolar bone. Notani 2: limited to the alveolar bone and/or above the level of the inferior alveolar canal. Notani 3: ORN under the lower part of the inferior alveolar canal, with fistula or bone fracture

As the primary endpoint of the trial is dependent on the availability and quality of radiographs and clinical photographs, a quality-control protocol is adopted. All new centres recruiting patients will have the first sets of images audited, and then 10% thereafter. These will be scored as adequate/inadequate to assess the presence of ORN by an appropriate panel assembled, viewed independently by three qualified clinicians, on reviewing anonymised images. Any centres submitting photographs of inadequate standard will be offered advice and training.

The schedule of enrolments, interventions and assessments is summarised using the Standard Protocol Items: Recommendations for Interventional Trials (SPIRIT) schedule as Fig. 3; and the SPIRIT Checklist provided as Additional file 1.

**Fig. 3 Fig3:**
[figure not shown]
Standard Protocol Items: Recommendations for Interventional Trials (SPIRIT) trial schedule

### Safety and adverse event reporting

Standard definitions and procedures for the management of adverse events (AE), serious adverse events (SAE), serious adverse reactions (SAR) and suspected unexpected serious adverse reactions (SUSAR) are adopted within the trial. AEs and reactions are reported using relevant Case Record Form (CRF), whether related to treatment or disease, within 28 days following the last trial treatment. This will be antibiotics and mouthwash in the control arm, and HBO in the treatment arm. In addition, a new diagnosis of cancer or recurrence of cancer will be reported as an SAE for the duration of the patient’s involvement in the study up to 12 months after surgery, irrespective of whether this is related to head and neck cancer, or the original indication for radiotherapy.

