### Trial intervention and control treatments

The supplier of the oxygen to be used will be dependent on standard practice within each hyperbaric unit. Treatment will be administered based around a version of the Royal Navy Therapeutic Table 66 – Repeat Hyperbaric Oxygen Therapy [22]. The patient undergoes pressurisation to 2.4 ATA at a tolerable rate. The patient undergoes decompression after 100% oxygen has been breathed at 2.4 ATA for a total of between 80 and 90 min. Air breaks while at 2.4 ATA may be introduced routinely or as required. The decompression is scheduled to control satisfactorily any risk to the patient and, if present, to the in-chamber attendant. Patients should breathe oxygen at an inspired partial pressure greater than 2.0 ATA for no more than 110 min during each individual treatment.

Patients in both arms of the trial are given chlorhexidine mouthwash and antibiotics. Pre- and post-operative chlorhexidine mouthwash 0.2% is used in a volume of 10 ml (i.e. one capful) washed around the mouth for around 1 min and spat out, three times daily (tds) for 5 days post-operatively. In case of chlorhexidine allergy, warm salt mouthwash at 1 teaspoon per cup of warm water is used. Orally administered antibiotics comprise amoxicillin 3 g 1 h pre-operatively (or 1 g administered intravenously) and 250 mg tds for 5 days post-operatively. In case of penicillin allergy this will be: 600 mg orally administered clindamycin (either 600-mg tablets orally (or the same dose of a 75-mg/5 ml suspension if tablets not tolerated) given 1 h pre-operatively (or 600 mg administered intravenously at the time of surgery) and 200 mg metronidazole orally tds for 5 days post-operatively.

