### Outcome measures

The primary outcome measure is the diagnosis of ORN 6 months following surgery as determined by a blinded central review of clinical photographs and radiographs as well as the site investigator’s assessment. This blinded review is carried out by an expert panel, with access to paired clinical photographs and radiographs (orthopantomogram). Additionally, where possible, any area of exposed bone is presented in context of an in-field rule and/or site investigator’s measurement on the case report forms. The diagnosis of ORN at 3 and 12 months are secondary outcome measures, but determined in a similar way, the only difference being that radiographs will only be taken at these time points if ORN has been clinically diagnosed. A summary of the outcome measures and their time points is presented in Table 2.

**Table 2 Tab2:** Outcome measures, time of assessment and method of assessment

Outcome measure	Timing	Method of assessment
Primary outcome		
Presence of ORN	6 months	Blinded review of radiograph, clinical photograph with corroboration from site investigator’s assessment in CRF (and dimensions of any exposed bone)
Secondary outcomes		
Presence of ORN	3 and 12 months	As primary endpoint, but without radiographs unless ORN clinically evident
Severity of ORN	3, 6 and 12 months	Blinded review of radiograph, clinical photograph, site investigator’s assessment (and dimensions of any exposed bone) using modified Notani Score [23, 24]
Quality of life	3, 6 and 12 months	University of Washington head and neck cancer questionnaire
Pain following surgery	3, 6 and 12 months	Patient-reported on a Visual Analogue Scale and use of analgesia
Acute symptoms	Days 1 thru 7 post surgery	Patient-reported Likert scale for pain, swelling, trismus, normalcy of diet
Assessment of implants (where relevant)	At closure of trial	Casenote review, by loss of any implant placed as part of trial
Late follow-up of MBS cases (where relevant)	At closure of trial	Casenote review, by severity of ORN using modified Notani Score [23, 24].
Safety of HBO related to cancer recurrence	Within 12 months of trial treatments	SAE reporting.
Safety of HBO, otherwise	Within 28 days of HBO	AE/ SAE reporting of symptoms related to hyperbaric treatment

*AE* adverse event, *CRF* Case Record Form, *HBO* hyperbaric oxygen, *MBS* minor bone spicules, *ORN* osteoradionecrosis, *SAE* serious adverse event

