The need for a blinded trial using sham treatments is considered desirable in trials where the primary endpoint is subjective or employ patient-reported outcome measures. In the HOPON trial the primary outcome is the presence of ORN, which is considered more objective, and additionally can be assessed on clinical photographs and radiographs at a remote time and location, by a panel of investigators who *are* blinded to the treatment arm received. However, the unblinded trial design for HOPON does introduce the possibility of reporting bias in some of the more subjective secondary outcomes such as quality of life or pain. Further, the unblinded design of the trial and need for extra treatments in the HBO arm introduces an inequality in time between randomisation and surgery for that arm. This potential methodological concern means that the time points commence at the time of surgery, rather than the date of randomisation, where it might be argued that only at randomisation are the two groups truly comparable.

Another difficulty that has arisen during the feasibility stage of the trial is the difficulty in robust allocation of some early stages of ORN. These have subsequently been classified as minor bone spicules (MBS), but are not reflected within any of the classifications of ORN currently in use. This difficulty is presumably not unique to the HOPON trial, yet it is difficult to ascertain from other similar studies how such cases have been dealt with. This is a problem created by taking a working ‘textbook definition’ of a clinical condition and extrapolating it as a primary outcome measure in a clinical trial. Because of the frequent (19%) finding of MBS during a blinded interim data review, it was logical to introduce an additional class to reflect this, the justification for which has been separately published [24]. To establish if any of the MBS cases in the HOPON trial will progress to clinically significant ORN, there is a secondary outcome measure of outcome of such patients at the conclusion of the trial. As a means to avoid any ambiguity, therefore, the use of the Notani classification with the additional category of MBS has been employed in order to avoid subjectivity and to enhance reliability and consistency of reporting.

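### General adverse events are collected over windows anchored differently by arm, and cancer recurrence has two conflicting end points

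*Protocol article*

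**What the plan says.** All references are to the protocol article.

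- **General AEs** (Safety and adverse event reporting). Events are reported "whether related to treatment or disease, within 28 days following the last trial treatment". The last trial treatment is then defined by arm: "This will be antibiotics and mouthwash in the control arm, and HBO in the treatment arm". The start of the window is not given.
- **Background treatment** (Trial intervention and control treatments). "Patients in both arms of the trial are given chlorhexidine mouthwash and antibiotics". The standard oral antibiotic runs at "250 mg tds for 5 days post-operatively"; the mouthwash and the penicillin-allergy alternative also stop at 5 days.
- **HBO safety** (Table 2). The outcome is AEs and serious AEs for symptoms related to hyperbaric treatment, up to 28 days from HBO.
- **Cancer recurrence.** Table 2 gives "Within 12 months of trial treatments". The safety section covers the patient's "involvement in the study up to 12 months after surgery".
- **Time to surgery** (Discussion). The design "introduces an inequality in time between randomisation and surgery for that arm", meaning the HBO arm. The Analysis plan adds that feasibility data showed somewhat more dropout after randomisation in that arm.
- **Implants** (Table 2). Assessed at trial closure: "Casenote review, by loss of any implant placed as part of trial".
- **Testing** (Analysis plan). Secondary endpoints get two-sided 5% tests with 95% intervals. Table 2 lists the safety items among the secondary outcomes.

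**The concern.** An AE count depends on how long one looks. If the two arms are observed for different lengths of time, or over different parts of the surgical course, a difference can appear or be hidden without any effect of HBO. Here a common anchor was available, because both arms take the same 5-day post-operative course, but the article uses it in the control arm only. Table 2's HBO-based window cannot be applied to controls at all.

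Recurrence is the oncological safety question about HBO, and it needs one clock. The article gives two. The surgery-based one leaves no end date for patients who never reach surgery, and these are likely to be more frequent in the HBO arm.

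**Working it through.** The article gives no figure for these windows, so there is none to reproduce. The only design figure borrowed is 103 per arm, which does reproduce (5% v 18.5%, 80% power, continuity-corrected two-proportion formula).

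**1. AE window on two clocks**

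Inputs from the article: antibiotics and mouthwash end on day 5 after surgery; reporting continues for 28 days; the Background calls 30 compressions typical. Assumed: 7 or 5 sessions a week, so a course of 30 or 30/5 × 7 = 42 days; last session between surgery and day 14 after it. The article gives neither the weekly schedule nor the split of sessions around surgery.

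| Clock | Control | HBO |
|---|---|---|
| From first treatment | 5 + 28 = 33 days (34 counting the pre-operative dose day) | 30 + 28 = 58 to 42 + 28 = 70 days |
| Closing day after surgery | 5 + 28 = day 33 | 0 + 28 = day 28 to 14 + 28 = day 42 |

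On the first clock the ratio is 58/33 = 1.76 to 70/33 = 2.12. On the second, the HBO window closes between 5 days before and 9 days after control's.

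**2. What this does to a comparison with no true effect**

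Assume the same constant daily hazard in both arms and a control risk r over 33 days (10% or 20%, assumed). The risk over w days is 1 − (1 − r)^(w/33).

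- First-treatment clock, r = 20%: 1 − 0.8^(58/33) = 32% to 1 − 0.8^(70/33) = 38%, against 20%.
- First-treatment clock, r = 10%: 17% to 20%, against 10%.
- Surgery clock, r = 20%: 1 − 0.8^(28/33) = 17.2% to 1 − 0.8^(42/33) = 24.7%, against 20%.

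The chance of a nominal p < 0.05 is Φ{[√n·|pH − pC| − 1.96·√(2p̄(1 − p̄))] / √(pC(1 − pC) + pH(1 − pH))} with n = 103. On the first-treatment clock this is about 53% to 81% at r = 20% and about 31% to 52% at r = 10%. A constant hazard is a simplification, since events will cluster around surgery.

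**3. Recurrence**

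Assume equal hazards, a 12-month risk of 5% to 20%, a control wait of 1 month to surgery, and 4 to 12 extra weeks in the HBO arm. If counting starts at randomisation and ends 12 months after surgery, control is at risk for 13 months and the HBO arm for 13 + 4 × 12/52 = 13.9 to 13 + 12 × 12/52 = 15.8 months.

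- At 10% per 12 months: 10.8% in control against 11.5% to 12.9%, ratio 1.07 to 1.20.
- Over 5% to 20%: ratio 1.06 to 1.21.
- Counted from surgery in operated patients: 12 v 12 months, ratio 1.00.

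**4. Implants**

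At an assumed 5% loss per year, cumulative loss is 5% at 12 months and 1 − 0.95^5 = 22.6% at 60 months. One figure read at closure mixes such follow-up times. The mixture varies by patient, and nothing in the article makes it differ materially by arm.

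**The case against.** Collecting AEs until a fixed time after each arm's own last treatment follows exposure, and oxygen is the investigational product. Table 2's HBO safety outcome concerns hyperbaric symptoms, which have no counterpart in control and need no matched window. No between-arm AE test is spelled out, and an analysis plan could restrict one to a shared sub-window. On recurrence, the safety section gives both arms the same end point, limits reporting to the patient's involvement in the study, and the Discussion openly discloses the unequal wait and says that time points start at surgery.

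Much of this stands. A descriptive HBO-arm listing of hyperbaric symptoms is sound, and a surgery-based clock gives operated patients equal recurrence windows. It does not remove the point. General AE collection covers events regardless of cause, the safety items sit among the secondary outcomes that receive 5% tests, and analysis cannot recover events that the reporting rule did not collect. The two recurrence anchors remain different.

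Three stronger readings are tempting:

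- *The HBO arm will show about twice the AEs.* This needs reporting to start at first treatment and a particular weekly schedule, neither of which is stated. Counted from surgery, the HBO window may even be the shorter one.
- *The recurrence comparison is biased.* That follows only if counting starts at randomisation, which neither place states.
- *Implant loss is biased.* Randomisation is 1:1 and stratified by centre, so follow-up at closure should be nearly balanced. Table 2 says when casenotes are read; it does not fix a crude proportion as the analysis.

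**Conclusion.** The point holds for AEs and, more narrowly, for recurrence.

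For AEs, the windows are unequal by the article's own definition. The direction and size are not determined by it: from first treatment the HBO window is roughly 1.8 to 2.1 times as long; from surgery it may end slightly earlier or later than control's. These figures rest on 30 sessions at 5 to 7 per week and on the assumed day of the last session. The event rates in the illustration are also assumptions.

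For recurrence, the two stated anchors must be reconciled, and unoperated patients have no surgery-based end date. The ratio of 1.06 to 1.21 is conditional on counting from randomisation and on the assumed delays.

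Implant loss is a matter of interpretability only. The primary endpoint, ORN at 6 months after surgery, is not touched.

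**What to change.** - **AEs.** Compare arms over one window on one clock, for example surgery to a fixed day in both arms, and list events during the HBO course separately for that arm. Put this in the reporting rule as well as the analysis, so that collection reaches the chosen day for everyone operated on.
- **Recurrence or new cancer.** Reconcile Table 2 with the safety section. Analyse all randomised patients by allocated arm, as time from randomisation to event with one common cut-off, so that patients who never reach surgery are included.
- **Implants (optional).** Report time from placement to first loss, censored at the last casenote entry.

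The cost is mainly wording, with slightly more data handling. Patients who leave before surgery need status up to the cut-off or must be censored at last contact. Follow-up after HBO within a common cut-off from randomisation will be somewhat shorter in the HBO arm, by about the extra wait for surgery. Later events fall outside the comparison but should still be listed.

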## Statistical considerations

### Sample size

Assuming an ORN rate of 5% in the HBO arm at 6 months following surgery consistent with an earlier RCT [10], 103 evaluable patients per group would provide 80% power to detect an odds ratio of 0.23 (equivalent to detecting an absolute difference of 13.5% between treatment arms) at a 5% two-sided significance level. An estimated dropout rate was extrapolated from feasibility data at 7%, resulting in an estimate of 221 patients to be recruited in total.

### Interim analyses

A feasibility stage was incorporated into the original funding application with endpoints of ability to recruit, randomise and complete trial protocols for 50 patients within 2 years of commencement. Following this, regular analyses of trial data by the Independent Safety Data Monitoring Committee (ISDMC) review occur at 12-monthly intervals to assess recruitment rates and toxicity. A single, formal interim analysis will be carried out when 100 dental extraction patients have been followed up to the primary endpoint at 6 months. The Peto stopping rule will be implemented for the primary efficacy outcome (ORN rate at 6 months following surgery), and a futility analysis will also be carried out.

### Sensitivity analyses

These will consist of:Assessing the effects of assuming that:all pre-surgery dropouts would have developed ORNno pre-surgery dropouts would have developed ORNall pre-surgery dropouts would have developed ORN with risk for their armall pre-surgery dropouts would have developed ORN with mean risk across both armsAssessing the effect of adjustment in analysis of the primary outcome for radiotherapy dose, age, sex, tobacco and alcohol useInclusion of multiply imputed primary endpoint responses for all randomised patientsComparison of results using the site principal investigator’s (PI’s) original assessment of ORN (as with the primary analysis, this will include assessment of centre effects)Analysis of ‘blinded review’ ORN after including MBS vs excluding cases with only MBS

### Translational research

In addition to the routine trial assessments, translational blood samples will be taken either at the time of surgery, or at any time after randomisation. Sample collection kits will be sent to all participating sites and the samples collected and stored to Good Clinical Laboratory Practice (GCLP) standard at the University of Liverpool. These samples will be used at a future date to discover/evaluate potential biomarkers of the genomic determinants of ORN [25].

## Trial oversight and regulatory arrangements

### Trial Management Group (TMG)

This comprises the chief investigator (CI), other lead investigators (clinical and non-clinical) and members of the LCTU. The TMG will be responsible for the day-to-day running and management of the trial and will meet approximately monthly.

### Trial Steering Committee (TSC)

The TSC will consist of the TMG plus three independent members, two patient representatives and an independent chair. The TSC will provide overall supervision for the trial and provide advice through its independent chair. The ultimate decision for the continuation of the trial lies with the TSC.

### Independent Safety Data Monitoring Committee (ISDMC)

The ISDCM will be responsible for reviewing and assessing recruitment, interim monitoring of safety and effectiveness, trial conduct and external data. The ISDMC will first convene prior to trial opening and will then define frequency of subsequent meetings (at least annually). The ISDMC will provide a recommendation to the TSC concerning the continuation of the study.

### Sponsorship

The HOPON trial is co-sponsored by the University of Liverpool and Aintree University Hospitals NHS Foundation Trust.

### Registration

The HOPON trial is registered with the European Clinical Trials Database (EudraCT 2007-006225-27).

### Clinical trial authorisation

The HOPON trial uses oxygen which is classified by the Medicines and Healthcare Products Regulatory Authority (MHRA) as an Investigational Medicinal Product. The trial has received a clinical trial authorisation by the MHRA under the Medicines For Human Use (Clinical Trials) Regulations 2004 S.I. 2004/1031 (MHRA **r**eference: 04196/0010/001-0019).

## Discussion

Several areas of controversy have arisen during the development of the HOPON protocol. The first of these is the need for blinding. Some comparable trials in other fields of late radiation toxicity have used a sham HBO arm with the aim of producing a double-blind trial [26–28]. The sham HBO arm used in such trials varies considerably. One approach [26] utilises a breathing mixture of 9% oxygen and 91% nitrogen so that at 2.4 ATA, arterial PaO_2_ is similar to breathing 21% oxygen at ambient air pressure. This, however, still exposes patients to the documented risks of hyperbaric pressure, and is by some considered unethical because of the implied issues of safety without any chance of benefit. Another approach used 40% oxygen and 60% nitrogen [28] providing an alternative lower ‘dose’ of oxygen treatment and correlation of outcome rather than a true control arm. More recently [27, 29] sham HBO arm using air at 1.1 ATA [29] or 1.3 ATA [27] have been used to provide a minimal increase in partial pressure of oxygen (PpO_2_) while providing the sensations of compression. Regardless of mode of delivery, the provision of sham HBO treatments are equivalent in cost to those delivered on the treatment arm which, given finite resources, may impact the cost-effectiveness of such research. Finally, it is also uncertain whether the HBO chamber staff could ever be effectively blinded as they remain in control of the chamber. It is, therefore, possible that patients become unblinded when treated for over 30 treatment sessions, particularly as these sham treatments are delivered at a regular and different daily session to the oxygen treatments.

The need for a blinded trial using sham treatments is considered desirable in trials where the primary endpoint is subjective or employ patient-reported outcome measures. In the HOPON trial the primary outcome is the presence of ORN, which is considered more objective, and additionally can be assessed on clinical photographs and radiographs at a remote time and location, by a panel of investigators who *are* blinded to the treatment arm received. However, the unblinded trial design for HOPON does introduce the possibility of reporting bias in some of the more subjective secondary outcomes such as quality of life or pain. Further, the unblinded design of the trial and need for extra treatments in the HBO arm introduces an inequality in time between randomisation and surgery for that arm. This potential methodological concern means that the time points commence at the time of surgery, rather than the date of randomisation, where it might be argued that only at randomisation are the two groups truly comparable.

Another difficulty that has arisen during the feasibility stage of the trial is the difficulty in robust allocation of some early stages of ORN. These have subsequently been classified as minor bone spicules (MBS), but are not reflected within any of the classifications of ORN currently in use. This difficulty is presumably not unique to the HOPON trial, yet it is difficult to ascertain from other similar studies how such cases have been dealt with. This is a problem created by taking a working ‘textbook definition’ of a clinical condition and extrapolating it as a primary outcome measure in a clinical trial. Because of the frequent (19%) finding of MBS during a blinded interim data review, it was logical to introduce an additional class to reflect this, the justification for which has been separately published [24]. To establish if any of the MBS cases in the HOPON trial will progress to clinically significant ORN, there is a secondary outcome measure of outcome of such patients at the conclusion of the trial. As a means to avoid any ambiguity, therefore, the use of the Notani classification with the additional category of MBS has been employed in order to avoid subjectivity and to enhance reliability and consistency of reporting.

Further concerns were around how to deal with missing data, dropouts and the effect of differing complexity and length of treatment between the two arms. While ITT analysis is usual practice for the primary analysis in superiority trials, in this trial ‘analysing as randomised’ would not answer the clinical question which relates to a fixed time following surgery, in other words the intended primary analysis is essentially on a per-protocol or treatment-received basis. While unusual, this is one of the circumstances in which, as Piantadosi [30] has pointed out, too strict adherence to the ITT principle is unhelpful or inappropriate.

The HOPON trial design has, therefore, evolved through analysis of feasibility data and through blinded interim data analysis. This is the only formally conducted, multi-centre, RCT conducted in this field that the authors are aware of, and it is the first since Marx’s single-centre study [10] published over three decades ago. The trial will provide data on the incidence of ORN after dental extraction and implant placement as well as the effect of HBO on retention of implants. Importantly, HOPON will provide translational resource for future studies of the genomic determinants of ORN in a group of patients treated to a defined protocol.

